### Outcome measures

#### Primary outcome (measured at 1, 3, 6,9,12,15,18,21 and 24 months)

#### Quality of life

EQ-5D is a standardized generic instrument for use as a measure of health outcome. Applicable to a wide range of health conditions and treatments, it provides a simple descriptive profile and a single index value for health status. EQ-5D measures five dimensions of health-related quality of life (HRQOL): mobility, self-care, usual activities, pain/discomfort and anxiety/depression. EQ Visual Analogue Scale: The EQ VAS records the respondent's self-rated health status on a vertically graduated (0–100) visual analogue scale [13]. Quality of life assessment based upon the European Organization for Research and Treatment of Cancer Quality of Life questionnaire (EORTC QLQ C-30); EORTC QLQ C-30 incorporates nine multi-item scales: five functional scales (physical, role, cognitive, emotional and social); three symptom scales (fatigue, pain, nausea/vomiting); and a global health status/QOL scale. Six single-item scales are also included (dyspnoea, insomnia, appetite loss, constipation, diarrhoea and financial difficulties) [14].

#### Economic analysis

A cost-effectiveness analysis will be performed alongside the randomized controlled trial. A Markov model will be employed. If the trial reveals no difference in health outcomes or quality of life of the patients, a cost-minimization analysis will be carried out. If we reveal a difference in quality of life between the two groups, we will implement a cost-utility analysis. The economic evaluation will have a health care and societal perspective. Resources used in both treatment arms will be registered prospectively based on reports by the patients and on the hospital patient records. Costs related to consultations at the primary and secondary care level, both at baseline and up to 24 months after randomization, including direct medical costs, indirect costs (production losses), travel costs and patient-/family-related costs will be registered. Quality of life measurements will be collected both at baseline and at several time points during the intervention. A 3% discount rate will be used to discount future costs and benefits. The cost elements will include costs related to outpatient visits, GP visits, laboratory tests, radiographs/ultrasound, examinations due to suspected relapse, treatment of relapse, travelling/transportation, production losses, co-payments and other patient/family expenses. The net costs and outcomes of the two treatment options will be compared and presented as incremental cost-effectiveness ratios.

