**Discussion:**

There is an ongoing debate on the best method of follow-up for patients with CRC. Due to a wide range of follow-up programmes and paucity of randomized trials, it is impossible to draw conclusions about the best combination and frequency of clinic (or family practice) visits, blood tests, endoscopic procedures and radiological examinations that maximize the clinical outcome, quality of life and costs. Most studies on follow-up of CRC patients have been performed in a hospital outpatient setting. We hypothesize that postoperative follow-up of colon cancer patients (according to national guidelines) by GPs will not have any impact on patients' quality of life. Furthermore, we hypothesize that there will be no increase in SCEs and that the incremental cost-effectiveness ratio will improve.

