### Sample size

Sample size calculations are according to Campbell's guidelines [15]

Alpha and beta were set at 0.05 and 0.2 respectively and tests were two-sided. We hypothesize that patients followed up by their GP will have a minor to moderate increase in the Global QoL scores (EORTOC-QLQ C30). This moderate effect size equals an increase of 10 units on the Global QOL [16]. Patients with colon cancer (local disease) show a standard deviation of approximately 20 (global QOL) [16]. Allowing for a dropout rate of 20%, to detect this difference with confidence we required a total sample size of 170 patients. Sample size calculations based upon EQ-5D showed similar results [17].

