### Analysis

We will use the intention-to-treat principle when analysing data. Furthermore, we will employ Fayers guidelines to handle missing data [18]. Treatment arms will be compared with respect to potential covariates using continuous and categorical univariable analyses. These will include variables relating to patients (age, sex, comorbidities, cost), treatment (surgical resection, surgical complications, adjuvant therapy), tumour (Dukes's Stage), hospital surgical outpatient clinic (cost, patient satisfaction, QoL), GP practice (cost, patient satisfaction, QoL). The cost elements will include costs related to outpatient visits, GP visits, laboratory tests, radiographs/ultrasound, and examinations due to suspected relapse, treatment of relapse, travelling/transportation, production losses, co-payments and other patient expenses. The net costs and outcomes of the two treatment options will be compared and presented as cost-effectiveness ratios. If the trial reveals no difference in health outcomes or quality of life for the patients, a cost-minimization analysis will be carried out. If we find a difference in quality of life or overall survival rates between the two groups, we will use a cost-utility approach. The economic evaluation will have a societal and health care perspective.

The method of analysis, including adjusting for covariates will comply with the CONSORT statement [19]. The results will be expressed as odds ratios for binary outcomes, hazard ratios for time- to-event outcomes or mean differences for continuous outcomes with corresponding standard errors, 95% confidence intervals, and associated p-values. P-values will be reported to three decimal places with p-values less than 0.001 reported as p < 0.001. For all tests we will use alpha = 0.05 level of significance.

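### The form of the economic evaluation depends on an undefined finding of no difference, so a non-significant result would be treated as equal effects in the cost-effectiveness conclusion

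*Protocol article*

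**What the plan says.** The rule appears twice in the protocol article, in almost the same words. Under Outcome measures, Economic analysis: "If the trial reveals no difference in health outcomes or quality of life of the patients, a cost-minimization analysis will be carried out". Under Analysis: "If the trial reveals no difference in health outcomes or quality of life for the patients, a cost-minimization analysis will be carried out".

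The opposite branch is worded differently in the two places. Economic analysis has "If we reveal a difference in quality of life between the two groups, we will implement a cost-utility analysis". Analysis has "If we find a difference in quality of life or overall survival rates between the two groups, we will use a cost-utility approach".

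The Economic analysis section also makes a promise with no condition attached: "The net costs and outcomes of the two treatment options will be compared and presented as incremental cost-effectiveness ratios". It opens by announcing a cost-effectiveness analysis alongside the trial and a Markov model. The Abstract (Discussion paragraph) hypothesises that "the incremental cost-effectiveness ratio will improve", and the Background names the incremental cost-effectiveness ratio (ICER) as part of the study's purpose.

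The only criteria for a difference are in Sample size, "Alpha and beta were set at 0.05 and 0.2 respectively and tests were two-sided", and in Analysis, "For all tests we will use alpha = 0.05 level of significance". No margin or confidence-interval rule for similarity is given. Costs are a primary endpoint in the Abstract and part of the primary objective.

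**The concern.** Cost-minimization is justified when effects are known to be equal, or close enough for any remaining difference not to matter. Here it would be entered after failing to find a difference, in a trial sized to detect a 10-unit gain on Global QoL and not to show similarity. The step from not significant to equal fixes the effect difference at zero and removes its uncertainty from the cost-effectiveness conclusion.

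The branch is not a remote one. The authors expect no effect on quality of life, or similar to higher scores, together with lower costs. That pattern leads to cost-minimization, which produces no ICER, although an ICER is promised and is hypothesised to improve.

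The triggers do not match either. One section starts cost-utility on quality of life alone; the other adds overall survival, which is not among the listed outcome measures. Under the Economic analysis wording, a clinical difference without a quality-of-life difference has no clear branch.

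**Working it through.** **Step 1. The plan's own sample size.** Inputs from Sample size: difference 10, SD 20, two-sided alpha 0.05, power 0.80, dropout 20%, total 170. Allocation is not stated; 1:1 is assumed.

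- Per arm: 2 × (20 × (1.960 + 0.842) / 10)² = 62.8, so 63; total 126.
- With dropout: 126 / 0.8 = 157.5, so 158. The t-test version gives 128 / 0.8 = 160.

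The stated 170 is 10 to 12 patients above this. The gap is on the conservative side and does not bear on the present point. Evaluable patients are taken as 170 × 0.8 = 136, or 68 per arm.

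**Step 2. What a non-significant Global QoL result would mean.**

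- SE = 20 × √(2/68) = 3.43.
- 95% CI half-width = 1.96 × 3.43 = 6.7 units.
- A result just short of significance, at about 6.7 units, has a 95% CI from about 0 to 13.4. That range includes the 10 units the article calls a moderate effect.
- P(non-significant given true difference d) = Φ(1.96 − d/SE) − Φ(−1.96 − d/SE).

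| True difference (units) | P(non-significant), 136 evaluable | P(non-significant), 126 evaluable |
|---|---|---|
| 2 | 91% | 91% |
| 5 | 69% | 71% |
| 7 | 47% | 50% |
| 10 | 17% | 20% |

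**Step 3. The effect uncertainty that would be dropped, in QALYs.** The documents give no EQ-5D SD, correlation or value per QALY, so these are assumptions: SD 0.15 to 0.25 (central 0.20), correlation ρ between any two visits 0.5 to 0.7, 68 per arm, eight post-baseline visits averaged over 23 months, and 20,000 GBP per QALY.

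- Unadjusted half-width = 1.96 × SD × √(2/68) × √((1 + 7ρ)/8) × 23/12. At SD 0.20 this is 0.097 (ρ = 0.5) and 0.111 (ρ = 0.7). Across the SD range it is 0.072 to 0.138.
- Adjusted for baseline utility, the variance factor becomes (1 + 7ρ)/8 − ρ². At ρ = 0.5 it is 0.5625 − 0.25 = 0.3125; at ρ = 0.7 it is 0.7375 − 0.49 = 0.2475. At SD 0.20 the half-width is 0.072 and 0.064. Across the SD range it is 0.048 to 0.090.
- In money, adjusted: 0.048 × 20,000 = 960 GBP to 0.090 × 20,000 = 1,800 GBP. The figure is proportional to the assumed value per QALY: half that value gives 480 to 900 GBP, and double gives 1,920 to 3,600 GBP.
- For scale, the main Discussion cites 1,232 GBP per patient for the basic programme and 1,943 GBP with work-up of suspected relapse.

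**Step 4. The two sections side by side.**

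| Item | Economic analysis | Analysis |
|---|---|---|
| Cost-minimization if no difference in | health outcomes or QoL | health outcomes or QoL |
| Cost-utility if a difference in | QoL | QoL or overall survival |
| Ratio promised | incremental, unconditional | cost-effectiveness ratios, unconditional |

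**The case against.** The strongest reply is that the damage is limited. Resource use is recorded in both arms whichever branch applies, and Analysis promises mean differences with 95% CIs. The cost difference and its interval therefore do not depend on the switch. Quality of life and serious clinical events are reported in their own right, so a reader would still see a possible loss. All of this stands. A reader might infer that the rule makes the cost intervals too narrow, or that the GP arm would be declared preferable on cost alone. The documents support neither: no such decision rule is written, and only the combined cost-and-effect summary changes.

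It can also be said that reading no difference as non-significance is an inference. That is true, but the article offers no other criterion. The percentages in Step 2 concern a single scale, whereas the rule speaks of health outcomes or quality of life. They therefore overstate how often cost-minimization would be reached if a difference on any measure blocks it. They do show how little a non-significant result establishes.

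A third reply is that cost-minimization may be meant as an addition, since the cost-effectiveness analysis and the ICERs are announced without condition. The text permits that reading but does not state it, and the passages need reconciling in either case.

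Finally, the QALY figures rest on assumptions, and the cited programme costs come from an earlier model-based study, not from this trial's cost difference. This limits Step 3 to an order of magnitude.

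**Conclusion.** The rule is wrong as written and should be fixed. It is stated in two sections, so it is not a detail left to a fuller plan. It would allow an unproven equality to enter the cost-effectiveness conclusion as fact: a half-width of 6.7 units on Global QoL cannot exclude differences that the trial itself regards as relevant. The article also contradicts itself on whether an ICER will be reported and on what triggers cost-utility.

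The size in money is uncertain. With baseline adjustment and the assumptions in Step 3, the neglected uncertainty is about 0.05 to 0.09 QALYs either way, or roughly 960 to 1,800 GBP at the assumed 20,000 GBP per QALY. That is the same order as the cited programme cost. The tempting stronger statement, that the unexcluded health loss matches or exceeds the whole programme cost, is not supported: the adjusted range starts below 1,232 GBP and ends below 1,943 GBP. Even the unadjusted range starts at about 1,450 GBP (0.0725 × 20,000), inside the cited costs. Randomization, data collection and the separate estimates of QoL, events and costs are untouched.

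**What to change.** Delete the conditional sentences on cost-minimization and cost-utility in Economic analysis and in Analysis. Replace them with one within-trial cost-utility analysis, run whatever the QoL p-value:

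- QALYs from EQ-5D, adjusted for baseline utility, and costs, estimated jointly (for example by bootstrap over patients).
- Incremental cost, incremental QALYs and incremental net benefit, with 95% CIs, over a range of values per QALY.
- An ICER only where it is interpretable. With effects about equal its denominator is near zero and the ratio is unstable. The unconditional promise of ICERs and the hypothesis of an improved ICER should be reworded to match.
- Health care and societal perspectives as two runs of the same analysis.
- A statement that the Markov model serves only extrapolation beyond the trial, or that it is dropped.

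An alternative is to keep cost-minimization but allow it only after a pre-set equivalence or non-inferiority criterion is met. This is harder to sustain at the planned size. With 136 evaluable patients, SD 20 and no true difference, non-inferiority on Global QoL at one-sided 0.025 has 83% power for an assumed margin of 10 units and 31% for 5. Requiring the 95% CI to lie within ±10 has 66% power, and within ±5 it is impossible, because 6.7 exceeds 5.

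The preferred change costs wording and modest analysis work. EQ-5D and cost questionnaires are already collected at the same nine time points. The drawback is that the economic conclusion will carry wider stated uncertainty.

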**Methods and Design:**

Patients undergoing surgery for colon cancer with histological grade Dukes's Stage A, B or C and below 75 years of age are eligible for inclusion. They will be randomized after surgery to follow-up at the surgical outpatient clinic (control group) or follow-up by the district GP (intervention group). Both study arms comply with the national NGICG guidelines. The primary endpoints will be quality of life (QoL) (measured by the EORTC QLQ C-30 and the EQ-5D instruments), serious clinical events (SCEs), and costs. The follow-up period will be two years after surgery, and quality of life will be measured every three months. SCEs and costs will be estimated prospectively. The sample size was 170 patients.

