### Intervention

Patients are randomized to follow-up either by their GP (intervention) or at the surgical outpatient clinic. All patients will receive their first postoperative check-up at the hospital which performed the surgery (baseline, 1 month). A clinical examination will then be performed and information about the histology and the results of the surgery will be provided. If the patient gives informed consent, randomization is performed. Patients randomized to GP follow-up are referred to their GP. This referral contains information about the surgery and any complications, Dukes's staging, guidelines for follow-up and behavioural strategy in the case of a SCE.

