#### QOL questionnaires

The EQ-5D and EORTC-QLQ C30 questionnaires for the two-year follow-up period (at 1, 3, 6, 9, 12, 15, 18, 21, 24 month follow-up) are given to the patient at baseline examination.

Economic evaluation questionnaire: A questionnaire has been developed to enable calculation of costs related to patient examinations. This questionnaire is incorporated in the QOL questionnaire, and patients are requested to fill out the questionnaire at 1, 3 6, 9, 12, 15, 18, 21 and 24 months postoperatively. The cost elements will include patient- and family-related costs due to outpatient visits, GP visits, laboratory tests, radiographs/ultrasound, examinations due to suspected relapse, treatment of relapse, travelling, production losses, co-payments and other patient expenses.

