### Randomization

Randomization will be done at the 1-month check-up (baseline) after the patients have given informed consent. The randomization service is web-based and managed by the Norwegian University of Science and Technology. Patients are stratified according to the Dukes's staging and whether they have a stoma. Patients allocated to general practice follow-up may be referred back to surgical clinics at any point in the study; similarly, patients in the surgeon-led follow-up group are free to consult their GP at any time during the study.

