### Data gathering

Data are being collected for patients in the intervention and the control group in identical ways. QoL and "cost questionnaires" are sent every three months (after each follow-up appointment) by the patients to the trial centre up to 24 months postoperatively. These questionnaires are optically readable, data being consecutively collected in a trial database.

SCEs are registered via hospital chart review at 24 months postoperatively. This follow-up period will allow identification of most SCEs, since tumour recurrence typically occurs within two years of surgery [11].

The study has been approved by the Norwegian Data Inspectorate. All data will be handled with strict confidentiality, and study reports or presentations will maintain the anonymity of patients, surgeons, GPs and hospitals. Data collection will be complete by the end of 2010.

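### The cost window is counted from randomisation but questionnaires stop 24 months after surgery, and the month-1 baseline is listed as a primary-outcome time

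*Protocol article*

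**What the plan says.** All places are in the protocol article.

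- **Randomisation.** The section Randomization states: "Randomization will be done at the 1-month check-up (baseline) after the patients have given informed consent". The section Intervention gives the same time and places the visit at the operating hospital for everyone: "All patients will receive their first postoperative check-up at the hospital which performed the surgery (baseline, 1 month".
- **Cost window.** The section Economic analysis registers costs "both at baseline and up to 24 months after randomization". Its sources are patient reports and hospital patient records.
- **Questionnaires.** Under QOL questionnaires, the cost form is due at "1, 3 6, 9, 12, 15, 18, 21 and 24 months postoperatively", and the QoL instruments follow the same months. Under Data gathering, forms are sent "by the patients to the trial centre up to 24 months postoperatively".
- **Follow-up.** The abstract sets it at two years, counted from surgery.
- **Status of the endpoint.** The abstract names the primary endpoints as QoL, "serious clinical events (SCEs), and costs". The heading in Outcome measures that covers both QoL and the economic analysis reads "Primary outcome (measured at 1, 3, 6,9,12,15,18,21 and 24 months".

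**The concern.** Two statements about a primary endpoint do not fit together.

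First, the time origin differs. Economic analysis counts 24 months from randomisation, while the abstract, the questionnaire schedule and Data gathering count 24 months from surgery. Because randomisation comes one month after surgery, the two windows end a month apart. Hospital records could be read to the later date, but patient-reported items such as production losses and family expenses have no scheduled form beyond the earlier one, and neither has QoL. An incremental cost-effectiveness ratio could then combine cost components, and costs and effects, measured over different periods.

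Second, month 1 has two roles. It is called baseline in Intervention and Randomization, yet it stands in the list of primary-outcome times. Costs incurred before allocation cannot depend on the arm, so they carry no information about the intervention when treated as outcome. As a baseline covariate they can improve precision.

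**Working it through.** **Window.** The inputs are randomisation at month 1 after surgery (Randomization, Intervention), a stated cost window of 24 months from randomisation (Economic analysis), and the last form at month 24 after surgery (QOL questionnaires, Data gathering).

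- End of the stated cost window: 1 + 24 = month 25 after surgery.
- End of the questionnaires: 24 − 1 = month 23 after randomisation.
- Gap: 25 − 24 = 1 month, or 1/24 = 4.2% of the stated window.
- Of the nine scheduled forms, one falls at baseline and eight after it.

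Table 1 of the article schedules no visit between months 24 and 30. The uncovered month would therefore hold mainly unscheduled contacts, work-up or treatment of relapse, and production losses.

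**Role of month 1.** The article gives no cost SD, so the effect of summing month-1 cost into the total can only be shown under assumptions. Let *s* be the SD of month-1 cost divided by the SD of post-randomisation cost, and ρ their correlation. Randomisation makes the expected month-1 difference between arms zero, so the expected total difference is unchanged. The standard error is multiplied by √(1 + s² + 2ρs):

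| s | ρ = 0 | ρ = 0.5 |
|---|---|---|
| 0.10 | √1.01 = 1.005 | √1.11 = 1.054 |
| 0.25 | √1.0625 = 1.031 | √1.3125 = 1.146 |
| 0.50 | √1.25 = 1.118 | √1.75 = 1.323 |

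The range is 0.5% to 32%. If month-1 cost is left out of the sum, the loss is zero. If it is used as a covariate, the standard error is multiplied by about √(1 − ρ²): 1.00 at ρ = 0 and √0.75 = 0.866 at ρ = 0.5.

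The planned total of 170 was sized on QoL, not on costs. The window finding does not depend on it.

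**The case against.** The strongest reply is that the article never adds month-1 values to an outcome. Economic analysis says that costs will be registered, which is data collection, and it mentions baseline apart from follow-up. The primary-outcome heading can be read as a measurement schedule that happens to include baseline. How a baseline value enters the model is usually left to the analysis plan, which is not shown, and the Analysis section already mentions covariate adjustment. The recall period of the month-1 form is not given, so it may cover little more than the baseline visit. All of this stands. A reader might infer that the plan puts pre-randomisation noise into the cost comparison, but the document does not support that as a statement of fact.

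A reader might also infer a loss of QoL power. Averaging over nine times would dilute a 10-unit effect to 10 × 8/9 = 8.9. With SD 20 and 170 × 0.8 / 2 = 68 per arm, power would appear to fall from 82.5% to 73%. This does not hold. No passage averages QoL over nine times, and a nine-time mean does not have the SD of a single measurement. With an assumed equal within-patient correlation ρ, its SD is 20 × √((1 + 8ρ)/9), or 14.9 at ρ = 0.5 and 17.1 at ρ = 0.7. Power is then about 93% and 85%, above 82.5%.

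On the window, it is fair to say that the gap is one month, that the same schedule applies to both arms, and that hospital records could fill part of it. The records would not supply patient-reported costs or QoL, however, so the contradiction remains. Because it lies between statements in the article itself, it cannot be put down to condensation.

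**Conclusion.** The point holds in two parts. The cost window contradicts the follow-up and questionnaire schedule by one month (24 against 23 months after randomisation), on an endpoint that the abstract calls primary. Month 1 is also listed as a primary-outcome time although it is the baseline.

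The size is modest. The window gap is 4.2% of the stated period and affects both arms' schedules alike. The harm is an inconsistent period across cost sources and between costs and QoL, not a demonstrated bias between arms. Any loss of precision is conditional: 0.5% to 32% on the standard error if month-1 costs were summed, under SD ratios and correlations that are assumptions and not figures from the article. No loss of QoL power is claimed.

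Treating month 1 as baseline assumes that the form is completed at the randomisation visit and reflects the time up to it. The article does not state the recall period or whether the form is completed before the allocation is known.

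**What to change.** 1. Use one window for costs, QoL and EQ-5D: from randomisation (month 1) to 24 months after surgery. In Economic analysis, replace the count from randomisation with a count from surgery, and cut hospital-record costs at the same date as the questionnaires.
2. In the primary-outcome heading, name month 1 as baseline and months 3 to 24 as outcome times.
3. Leave month-1 cost out of the compared total. Adjust the cost, QoL and EQ-5D comparisons for their month-1 values.
4. Say what period the month-1 form covers and that it is completed before allocation is disclosed. If it is not, say so, because that limits its use as a baseline.

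The cost is wording in the protocol and analysis plan. The month-1 forms are already on the collection schedule, so no further data are needed. If the sponsor already intends this analysis, the change only makes the text say so.
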